## Abstract

**Background:**

Menstrual migraine (MM) is a neurological disorder affecting women of childbearing age. According to the definition in the International Classification of Headache Disorders, 3rd Edition (ICHD-3), it includes pure menstrual migraine (PMM) and menstrually-related migraine (MRM). The efficacy and safety of acupressure therapy for menstrual migraine have not yet been fully evaluated, particularly when administered sequentially according to specific phases of the menstrual cycle. Therefore, we designed this trial to preliminarily assess whether sequential acupressure therapy shows a favorable trend in efficacy compared with oral naproxen sodium, and to evaluate its feasibility, safety, and tolerability, thereby providing baseline data for future large-scale confirmatory trials.

**Methods:**

This is a randomized, active-controlled, parallel-group trial. A total of 76 eligible women aged 18–45 years with migraine without aura and diagnosed with pure menstrual migraine or menstrually-related migraine will be recruited and randomly allocated to receive either sequential press-needle therapy or oral naproxen sodium therapy. In the press-needle group, treatment is delivered at designated acupoints across two phases (pre-menstrual and post-menstrual) per menstrual cycle. Each phase includes 2 sessions with a 2-day interval (4 sessions per cycle), repeated for 3 consecutive cycles. In the control group, oral naproxen sodium (550 mg twice daily after breakfast and dinner) is initiated 2–3 days before the expected onset of menstruation and continued until menstruation ends (5–7 consecutive days per cycle), also for 3 complete cycles. Compliance is monitored by a daily medication diary and telephone follow-up. The primary outcome is the change in the number of headache days with a peak pain intensity of ≥4 (moderate-to-severe) on a 0–10 Numeric Rating Scale (NRS, where 4–6 = moderate, 7–10 = severe) per menstrual cycle from baseline to the end of the 3-month intervention. Secondary outcomes include headache intensity, functional impact, quality of life, acute medication use, and heart rate variability indices. Exploratory outcomes include serum biomarkers and resting-state functional MRI.

**Conclusion:**

This trial will evaluate the preliminary efficacy and safety of sequential press-needle therapy compared with oral naproxen sodium for menstrual migraine. The results will be used to estimate effect sizes and inform the design of future adequately powered confirmatory trials.

**Study protocol registration:**

https://itmctr.ccebtcm.org.cn/mgt/project/view/2049072453099061248, ITMCTR2025002153.

## Introduction

Menstrual migraine (MM) is a neurological disorder with a high prevalence that significantly impacts women’s lives; it is characterized by migraine attacks concentrated around the menstrual period. According to the International Classification of Headache Disorders, 3rd Edition (ICHD-3), MM can be subdivided into two distinct types: pure menstrual migraine (PMM, Appendix code A1.1.1) and menstrually-related migraine (MRM, Appendix code A1.1.2). PMM is defined as migraine attacks occurring exclusively between the second day before menstruation and the third day after menstruation in at least two of three consecutive menstrual cycles, with no attacks at other times during the menstrual cycle. MRM refers to attacks that occur both within this perimenstrual window and at other times of the cycle in at least two of three cycles (1). These two subtypes reflect fundamentally different temporal patterns of estrogen-withdrawal susceptibility and trigeminovascular sensitization. Epidemiological studies indicate that up to 60% of female migraineurs experience menstrual-related attacks, which are often more severe, longer in duration, and less responsive to conventional acute medications compared to non-menstrual migraines (2). These headaches substantially impair daily functioning, reduce quality of life, and contribute to absenteeism and socioeconomic burden (3).

The pathophysiological mechanisms of MM involve multiple factors and are primarily driven by a sudden drop in estrogen levels. This process modulates serotonergic and glutamatergic neurotransmission, triggers the release of calcitonin gene-related peptide (CGRP), and exacerbates cortical hyperexcitability and central sensitization (4, 5). Given the predictability of attack timing, short-term perimenstrual prophylaxis (SPP) is the recommended management strategy. International guidelines, including those from the European Headache Federation, identify naproxen sodium as the first-line drug choice for SPP, as it has recognized efficacy in reducing the frequency and severity of menstrual migraines through potent inhibition of peripheral and central cyclooxygenase-2 (6). However, long-term use of naproxen and other nonsteroidal anti-inflammatory drugs (NSAIDs) is associated with gastrointestinal intolerance, an increased risk of bleeding, and the potential to induce medication-overuse headaches (7, 8). This highlights an unmet medical need for the development of safe, well-tolerated, and effective preventive treatment options.

Acupuncture has been increasingly applied for migraine prophylaxis, with evidence supporting its effect in reducing headache frequency and intensity, possibly through modulation of pain-related brain networks, autonomic balance, and neuroinflammatory markers (9). However, most existing acupuncture protocols are fixed-point regimens that do not account for the cyclic nature of menstrual headaches. Sequential acupuncture tailored to the menstrual phase—pre-menstrual and inter-menstrual—may better align with the dynamic hormonal and neurovascular changes, potentially enhancing therapeutic efficacy (10, 11). Furthermore, a significant practical barrier to conventional acupuncture is the need for frequent clinic visits, which can be time-consuming, burdensome, and lead to poor long-term adherence. Press-needle therapy, characterized by its semi-permanent indwelling needles that patients can self-stimulate, drastically reduces the frequency of clinic visits while providing continuous therapeutic stimulation (12). This feature may address key limitations of traditional acupuncture by improving treatment convenience, patient compliance, and overall acceptability—a crucial factor for the successful management of a chronic, cyclical condition like menstrual headache. Nevertheless, high-quality randomized trials evaluating such time-sensitive acupuncture approaches are scarce.

Given the limitations of current treatments and the theoretical rationale for phase-specific intervention, we designed a randomized trial to evaluate the efficacy and autonomic effects of sequential press-needle therapy for menstrual migraine. This protocol integrates objective biomarkers, heart-rate variability, and patient-reported outcomes to comprehensively assess treatment response and explore potential mechanisms.

## Objectives

The efficacy and safety of acupressure therapy for menstrual migraines have not yet been fully evaluated, and most existing acupuncture trials for MM have employed fixed protocols without phase-specific adjustments. Furthermore, no study has systematically integrated objective autonomic nervous system function, serum biomarkers, and neuroimaging findings to comprehensively assess the mechanisms underlying acupressure treatment for MM. To address these limitations, we designed this randomized exploratory trial to:(1) Evaluate the feasibility of a phase-specific sequential acupuncture protocol;(2) Assess the preliminary efficacy and variability of pressure-point acupuncture compared with the standard naproxen prophylaxis regimen, providing an effect size estimate for future sample size calculations;(3) Explore potential mechanisms of action through multidimensional autonomic, serological, and neuroimaging markers.

Importantly, this trial is an exploratory rather than a confirmatory study. The findings will inform the design of future large-scale, definitive randomized controlled trials. We hypothesize that, compared with naproxen, sequential pressure-needle therapy will show a clinically favorable trend and demonstrate good safety and tolerability, and that the observed changes in autonomic nervous system and biomarker results will provide mechanistic insights for subsequent studies.

## Methods

### Trial design

This research protocol was designed in accordance with the requirements of the 2025 version of SPIRIT guidelines (13). The flowchart of the entire trial process is provided in Figure 1. This figure details the paths of participant recruitment, screening, randomization, intervention measures, assessment, and analysis, and visually compares the intervention plans and key time points of the two study groups.

**Figure 1 fig1:**
[figure not shown]
Flow chart for clinical trial procedure.

### Study participants

This single-center trial will be conducted at Chengdu Pidu District Hospital of Traditional Chinese Medicine. Participants will be diagnosed according to the ICHD-3 criteria. Eligibility assessment will be performed by board-certified neurologists or headache specialists. Written informed consent, obtained prior to any study procedures, is mandatory for enrollment.

### Eligibility criteria

#### Inclusion criteria

Meets the diagnostic criteria for “migraine without aura” (ICHD-3 code 1.1)” as defined in the International Classification of Headache Disorders, 3rd Edition (ICHD-3);Meets the diagnostic criteria for “pure menstrual migraine” (A1.1.1) or “menstrually-related migraine” (A1.1.2) as outlined in the appendix to the ICHD-3, and this diagnosis has been validated by a prospective headache diary covering three consecutive menstrual cycles;Age 18–45 years, with a normal menstrual cycle of 28 ± 7 days and a menstrual duration of 3–7 days;During the 3-cycle screening period, at least 2 of the 3 menstrual cycles have 2–14 days with moderate-to-severe headache (NRS ≥ 4) per cycle (meeting the ICHD-3 appendix criterion for PMM or MRM). Baseline data for the primary outcome will be calculated as the average number of moderate-to-severe headache days across all qualified cycles (i.e., those cycles meeting the 2–14 day criterion) during the screening period;Complete the daily headache diary throughout the 3-cycle screening period (with a completion rate of ≥80% for daily entries within each menstrual cycle) to demonstrate good patient compliance;Voluntary signing of the informed consent form.

#### Exclusion criteria

Primary diagnosis of other primary or secondary headache disorders (e.g., tension-type headache, cluster headache, migraine with aura, medication-overuse headache);Concurrent severe or unstable cardiovascular, cerebrovascular, hepatic, renal, or hematopoietic system diseases, or malignant tumors;Diagnosed with severe mental disorders such as major depressive disorder, anxiety disorder, or bipolar disorder;Currently pregnant, breastfeeding, or planning to become pregnant within the next 6 months;Use of hormonal contraceptives or other hormonal therapies affecting the menstrual cycle within the past 3 months; regular use of pain relievers, triptans, or ergotamine-based acute migraine medications for ≥10 days per month within the past 3 months; or receipt of migraine preventive medications, acupuncture, or other systemic non-pharmacological treatments within the past month;Presence of coagulation disorders, severe osteoporosis, or skin infection/lesions at the proposed acupuncture site; history of allergy or severe adverse reactions to acupuncture or press-needle therapy;Currently participating in other interventional clinical trials;Allergy to naproxen sodium or other NSAIDs; history of active gastrointestinal ulcers or gastrointestinal bleeding; or severe hepatic or renal insufficiency;Other conditions deemed by the investigator to preclude participation in the trial or pose significant safety risks.

#### Criteria for discontinuation of intervention

Occurrence of a serious adverse event (SAE) related to the study intervention;Confirmed pregnancy during the trial;Significant worsening of headache requiring emergency treatment or alternative therapy, as determined by the investigator;Voluntary withdrawal of consent by the participant;Lost to follow-up, with no contact possible for assessments or interventions;Major protocol violation (e.g., use of prohibited medications, non-adherence to intervention, compromising efficacy or safety evaluation);Development of a new medical condition contraindicating continued trial participation.

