#### Management of excluded, withdrawn, and discontinued cases

Documentation and Follow-up: All withdrawals or discontinuations will be fully documented. A follow-up will be performed to identify the reason for discontinuation. All previously collected data will be retained for analysis;Data Handling: Participants completing less than 50% of scheduled interventions will be classified as major protocol violators. Their data will be excluded from per-protocol analysis but may be included in intention-to-treat analysis for sensitivity testing;Adverse Event Management: Participants discontinuing due to adverse events or insufficient response will receive timely clinical care or referral as needed;Post-Trial Care: If the study intervention is ineffective, alternative treatment options may be discussed with the participant within ethical guidelines;Sample Size Maintenance: If the dropout rate exceeds the pre-specified threshold, additional participants will be recruited to maintain statistical power.

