### Relevant concomitant care: permitted and prohibited

### Permitted

Rescue medication: Paracetamol (acetaminophen) is allowed as the sole rescue medication for severe migraine attacks. Paracetamol was selected because (1) it has a distinct mechanism of action (central COX-2 inhibition) that does not interfere with the pharmacological effects of the prophylactic NSAID (naproxen sodium, a peripheral COX-1/COX-2 inhibitor); (2) it carries a significantly lower risk of medication-overuse headache (MOH) compared to triptans or combined analgesics (14), which is critical for maintaining the integrity of the primary outcome (headache frequency) over the 3-month intervention period; and (3) it is the most commonly used rescue analgesic in Chinese clinical practice with an established safety profile (15). NSAIDs (including naproxen sodium, except for the assigned prophylactic regimen), triptans, and ergotamines are strictly prohibited to avoid intervention overlap and medication overuse. All rescue medication use (dose and frequency) must be recorded in the daily headache diary, and participants will be instructed to limit paracetamol use to a maximum of 2 days per week to minimize the risk of analgesic overuse.

Non-pharmacological care: Only general lifestyle advice (hydration, sleep, stress management, diet) is permitted; no headache/menstrual-specific non-drug interventions (e.g., acupuncture, moxibustion, herbal medicine) are allowed.

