#### Analysis populations

Intention-to-Treat (ITT) Population: All randomized participants, analyzed according to their originally assigned group, regardless of protocol adherence or dropout.

Per-Protocol (PP) Population: A subset of the ITT population comprising participants who completed at least 80% of the planned treatment courses (all three cycles with 4 sessions per cycle), provided valid primary outcome data at the end of the intervention period, and had no major protocol violations.

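### The rule for discontinued cases makes ITT inclusion of poor adherers optional, contradicting the ITT definition; stopping treatment for protocol violations is a secondary, avoidable choice

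*Protocol article*

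**What the plan says.** **ITT membership.** Management of excluded, withdrawn, and discontinued cases sets a class: "Participants completing less than 50% of scheduled interventions will be classified as major protocol violators". It continues: "Their data will be excluded from per-protocol analysis but may be included in intention-to-treat analysis for sensitivity testing". Analysis populations defines ITT as "All randomized participants, analyzed according to their originally assigned group, regardless of protocol adherence or dropout". Statistical methods says that all analyses use both ITT and per-protocol principles. Subgroup and sensitivity analyses lists the per-protocol analysis, and ITT without imputation, among the sensitivity analyses.

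**Stopping treatment.** Criteria for discontinuation of intervention includes "Major protocol violation (e.g., use of prohibited medications, non-adherence to intervention, compromising efficacy or safety evaluation". Related serious adverse events, pregnancy, marked worsening of headache and new contraindications are listed there separately. On rescue treatment, the Permitted subsection says "Paracetamol (acetaminophen) is allowed as the sole rescue medication for severe migraine attacks". After naming NSAIDs outside the assigned regimen, it adds "triptans, and ergotamines are strictly prohibited to avoid intervention overlap and medication overuse". The per-protocol set takes only women who "provided valid primary outcome data at the end of the intervention period, and had no major protocol violations", besides meeting an 80% completion rule. For women who stop, the plan promises a contact to learn the reason and states "All previously collected data will be retained for analysis".

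**The concern.** The ITT set exists so that membership depends on randomisation alone. A rule that makes inclusion of poor adherers optional, and describes it as sensitivity work, lets the main estimate depend on a choice made after adherence is known. Poor adherence may be related to tolerability or lack of benefit, so that choice need not be neutral between arms.

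The stopping criterion raises a related but weaker issue. Objectives and Sample size make feasibility, retention and an effect-size estimate the purpose of this pilot. If the protocol itself ends treatment for non-adherence or for a prohibited drug, some discontinuations are imposed by the rule. Because paracetamol is the only permitted rescue drug, prohibited-drug use can follow poor response. A woman stopped before cycle 3 has an off-treatment or missing value at Month 3, where the primary contrast is read.

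**Working it through.** **1. The plan's own figure.** 30 per group with 20% dropout: 30 / (1 − 0.20) = 37.5, rounded up to 38; 2 × 38 = 76. This reproduces and is not in dispute.

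**2. The ITT rules side by side.** The press-needle schedule is 3 cycles × 4 sessions = 12. Under 50% means fewer than 6, so 5 or fewer. Take a woman with 5 sessions.

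- Analysis populations: in ITT, unconditionally.
- Statistical methods: ITT applies to all analyses, so she is in the primary one.
- Management of excluded, withdrawn, and discontinued cases: she may be in ITT, for sensitivity testing.

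The per-protocol part of that last sentence adds nothing for her. The 80% rule needs 0.80 × 12 = 9.6, so 10 or more sessions, and she is already out. The ITT clause is the only part of the sentence that could change where her data go, and it conflicts with the definition. The 50% and 80% thresholds do not contradict each other.

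**3. How many women the 50% class could hold.** No miss rates are given, so these are assumptions. A press-needle woman falls in the class at 7 or more misses out of 12.

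| Assumed miss rate | Independent misses | Clustered misses (assumed intraclass correlation 0.4) |
|---|---|---|
| 10% | 0.005% | about 6% |
| 20% | 0.4% | about 14% |
| 30% | 3.9% | about 24% |

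Of 38 women, that is about 0, 0.2 and 1.5 with independent misses (38 × 0.004 = 0.15; 38 × 0.039 = 1.5). With clustering it is about 2, 5 and 9 (38 × 0.06, 0.14 and 0.24).

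**4. What the stopping rule does to recorded adherence.** Suppose treatment stops at the seventh miss, using the 50% line, although the plan does not expressly tie that line to the stopping criterion.

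- Independent misses: mean attendance goes from 90.00% to 90.00%, 80.00% to 79.98% and 70.00% to 69.78%. The falls are 0.0, 0.02 and 0.2 points.
- Clustered misses: the falls are about 0.3, 0.8 and 1.2 points.

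The 50% line does not cover prohibited-drug stops. The arm has 38 × 12 = 456 sessions. A fully attending woman stopped after cycle 1 is recorded at 4/12 = 33%, and the arm mean loses 8/456 = 1.75 points. After cycle 2 she is at 8/12 = 67%, and the loss is 4/456 = 0.88 points. Either way 1/38 = 2.6% of the arm's Month 3 values is off-treatment or missing. The number of such women cannot be derived from the document.

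**The case against.** On ITT, the statistical sections are explicit and unconditional, and one listed sensitivity analysis does use ITT data, which may explain the loose phrase. A reader might infer that ITT membership is undecided throughout. It is not: the formal definition is clear and should prevail. What stands is that another section states an incompatible rule.

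On stopping, the opposing case has more force, and three stronger readings are not supported.

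- **That a single rescue triptan ends treatment.** The criterion requires a major violation that compromises evaluation. The lack of a numerical threshold is detail that an article may leave to the full protocol.
- **That outcomes are lost after a stop.** The heading concerns the intervention, not follow-up, and nothing says that the diary ends. Off-treatment values are legitimate ITT data, and multiple imputation with a delta-adjusted analysis is planned for missing ones.
- **That the effect estimate is biased by a given amount.** Any such figure would need stop rates and outcome differences that the document does not contain.

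Discontinuations and their reasons are to be documented, so imposed stops can be reported separately. Some response-related stopping would also remain under the worsening-headache criterion. What survives is that the rule withdraws treatment without being needed to protect the per-protocol set, and that neither ITT nor imputation restores that treatment.

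**Conclusion.** The ITT wording is wrong as written and should be corrected: one section makes optional what the definition makes mandatory. This conclusion rests on the text alone. The practical size depends on how many women complete under half the schedule, which the document does not say. Under the assumed miss rates it runs from essentially none to about 9 of 38 in the press-needle arm.

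Stopping allocated treatment for non-adherence or prohibited medication is a design choice, not an error. Its effect on mean attendance is small under the 50% line (at most about 1.2 points in the cases tried) and unknown for prohibited-drug stops. It stands as a cheap improvement only.

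**What to change.** **Main change**, in Management of excluded, withdrawn, and discontinued cases: state that women completing under 50% of interventions are included in the intention-to-treat analysis and are excluded only from the per-protocol analysis. This is one phrase and costs nothing.

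**Secondary change**, in Criteria for discontinuation of intervention: limit the violation criterion to violations that make continuing unsafe, for example an added NSAID on top of naproxen. Record other violations as dated deviations with reasons, to be used for the per-protocol set. Keep offering the allocated schedule, and state that the diary continues after any stop.

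The diary and the concomitant-medication review in Table 2 already collect what is needed. The real cost is somewhat more off-protocol medication in the ITT data, including NSAIDs, the comparator's class, in the press-needle arm. That could pull the contrast towards no difference, so such use should be reported by arm.
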